**Objective:**

The main objective of this study is to investigate to what extent a reduction in impulsivity by a sensorimotor rhythm (SMR)-neurofeedback intervention will lead to a reduction in craving in a population of forensic psychiatric patients with a diagnosis of SUD.

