
### Objectives

Primary outcome variables are the degree of impulsivity as measured with the Dutch version of the BIS-11 [39]; inhibitory control as measured with a cued go/no-go reaction time task [40]; degree of drug craving as measured with an altered version of the Desire for Alcohol Questionnaire (DAQ) [41]; actual drug use as measured with urine, saliva, or breathalyzer analysis; and changes in resting state EEG pattern.

Primary objective: To what extent does a reduction in impulsivity by using SMR-neurofeedback result in a reduction of core symptoms of SUD such as craving and actual drug use in a population of forensic psychiatric patients with a diagnosis of SUD?

Secondary objectives:

1. To what extent can an SMR-based neurofeedback intervention reduce levels of impulsivity as measured by BIS-11 and a cued go/no-go task in a population of forensic psychiatric patients with a diagnosis of SUD?

2. To what extent can an SMR-based neurofeedback intervention reduce levels of craving as measured by self-report questionnaire DAQ-SF (short form) in a population of forensic psychiatric patients with a diagnosis of SUD?

3. To what extent can an SMR-based neurofeedback intervention reduce actual drug use as measured with urine, saliva, or breathalyzer analysis in a population of forensic psychiatric patients diagnosed with SUD?

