### Participants

A power analysis calculation for the RCT using G*Power 3 (Department of Psychology) based on a 1-tailed alpha value of .05, a power value of 0.80, and an effect size (*f*) of 0.80 yielded a recommended sample size of 21 participants each in the control and intervention conditions. Given the special research population we aim to select 25 participants for each condition.

Participants are male patients diagnosed with SUD (substance dependency or substance abuse) according to the *Diagnostic and Statistical Manual of Mental Disorders*, Fourth Edition, Text Review (DSM-IV-TR [43]) and currently staying at the treatment facility. Participants have tested positive for drug use in the past 24 months at time of inclusion. Drug use is operationalized as urine, saliva, or breathalyzer analysis testing positive for either marijuana and/or psychostimulant/opioid drugs and/or alcohol. Corresponding with treatment facility policy, nonprescribed medication that is used for recreational drug consumption such as inhaled methylphenidate will also be scored as positive drug testing, as will refusal to undergo drug testing.

Participants are allowed to continue using prescription medication (as prescribed by a psychiatrist or general physician of the treatment facility) but are required to inform researchers of any medication they are currently using or any change in medication during treatment with neurofeedback.

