#### Cued Go/No-Go Task

The cued go/no-go task is a continuous performance test measuring impulse control by the ability to inhibit prepotent responses [40]. Participants are instructed to respond to a green square by pressing a button as quickly as possible while not responding to a blue square. A go or no-go cue is given before the actual target appears, providing information about the likelihood of an actual go or no-go target [40]. The likelihood of a correct target after a cue is manipulated with a 80/20 ratio, with 80% being a correct cue and 20% being an incorrect cue. Cues are presented with 4 fixed stimulus onset asynchronies (100, 200, 300, and 400 ms), giving participants time to prepare for responding. The cued go/no-go task has been proven to be a useful measurement of impulse control in substance abusing populations [40]. It consists of 250 trials spread over 5 rounds with a 30-second break between each round, taking approximately 20 minutes to complete. Outcome measurements are omission (the participant does not respond when he should respond) and commission errors (the participant responds when he should not respond) and reaction time.

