#### Randomized Controlled Trial

Resting state EEG data will be analyzed using custom-made Matlab R2012b scripts [51]. A repeated measures multivariate analysis of variance with factors condition (neurofeedback vs control) and frequency band (delta, theta, alpha, beta, or gamma) will be conducted. If main or interaction effects are observed, post hoc tests will be used to determine which levels of the factors are explaining the observed effects.

Repeated measurement with time (pre- [T0] and postintervention [T1]) as the within-subject factor and group (control vs intervention) as the between-subject factor will be conducted for the DAQ-SF, BIS-11, IFTE, and IFTE-SR. If main or interaction effects are observed, post hoc test will be used to determine which levels of the factors are explaining the observed effects. A repeated measures analysis of covariance will be conducted to examine differences in actual drug use as dependent variables to test for a moderating effect of impulsivity on craving and actual drug use.

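### Five unranked primary outcomes conflict with the stated objectives, and the RCT analysis follows up any main or interaction effect without naming the treatment contrast

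*Protocol article*

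**What the plan says.** **Outcomes and objectives.** The Objectives section opens its list with "Primary outcome variables are the degree of impulsivity as measured with the Dutch version of the BIS-11". It goes on to the cued go/no-go task and the altered DAQ, and ends with "actual drug use as measured with urine, saliva, or breathalyzer analysis; and changes in resting state EEG pattern". That makes five primary outcomes, with no order among them. The same section makes the primary objective a question about whether reduced impulsivity lowers craving and drug use. The direct effects of neurofeedback are secondary objectives, the first being "To what extent can an SMR-based neurofeedback intervention reduce levels of impulsivity as measured by BIS-11 and a cued go/no-go task"; craving and drug use follow. EEG appears under no objective. The abstract's main objective is that reduced impulsivity "will lead to a reduction in craving in a population of forensic psychiatric patients with a diagnosis of SUD".

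**Analysis (Statistical Analysis, Randomized Controlled Trial).**
- DAQ-SF, BIS-11, IFTE and IFTE-SR get a time-by-group repeated measures analysis, with the rule "If main or interaction effects are observed, post hoc test will be used to determine which levels of the factors are explaining" the observed effects. Only the first two are primary.
- Resting EEG gets a repeated measures MANOVA with condition and frequency band as the listed factors and a matching rule. Time is not listed.
- Drug use gets a repeated measures ANCOVA, described as a test of moderation.
- The go/no-go task is not named in this section. Under Measures it yields several scores: "Outcome measurements are omission (the participant does not respond when he should respond) and commission errors", plus reaction time.

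**Alpha.** The only significance level stated is in the sample size paragraph: "based on a 1-tailed alpha value of .05, a power value of 0.80".

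**The concern.** Two things are left unsettled. First, a reader cannot tell which outcome decides the trial. The list of primary outcomes, the primary objective, the secondary objectives and the abstract give different answers, and the sample size paragraph does not say which outcome it serves.

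Second, the analysis section never says which term in the 2×2 model is the test of neurofeedback. All participants stay on active usual treatment, which can include relapse prevention, so both arms may improve. That would appear as a main effect of time and would meet the condition for follow-up. A main effect of group averages over T0 and T1, so a chance imbalance at T0 feeds into it. Neither is evidence that neurofeedback works. Time and group have two levels each, so a post hoc test of either main effect also adds nothing to the main effect itself.

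At stake is a report that can draw on whichever primary outcome, and whichever term, reached significance.

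**Working it through.** **1. The plan's own figure.** Inputs from Participants: one-tailed 0.05, power 0.80, effect size 0.80, and a result "of 0.80 yielded a recommended sample size of 21 participants each in the control and intervention conditions". A two-sample t-test with noncentral t and standardised difference d = 0.80 gives n = 21 per arm (power 0.817). The figure reproduces as one one-tailed comparison of two means, with 0.80 read as d; the text labels it f. It contains no allowance for several primary outcomes. The document states no family-wise error rate, so there is none to reproduce.

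**2. What each term estimates.** Write the cell means as N0, N1 (neurofeedback) and C0, C1 (control).
- Group by time: (N1 − N0) − (C1 − C0). This is the randomised comparison of change.
- Time: [(N1 − N0) + (C1 − C0)]/2. It is non-zero whenever both arms change equally.
- Group: [(N0 + N1) − (C0 + C1)]/2. It includes half of any T0 difference.

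**3. False-positive rate for the treatment contrast.** Assumptions: each outcome tested once at 0.05, 25 per arm, no true effect. The document gives no between-outcome correlation, so a range is shown.
- Five independent tests: 1 − 0.95⁵ = 0.226. Two: 1 − 0.95² = 0.0975.
- Simulation, 40,000 runs per case:

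| Correlation between outcomes | Five outcomes | BIS-11 and DAQ-SF only |
|---|---|---|
| 0 | 22.4% | 9.8% |
| 0.3 | 20.8% | 9.7% |
| 0.5 | 18.4% | 9.3% |
| 0.7 | 14.9% | 8.3% |
| 0.8 | 13.1% | 7.9% |

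- One designated outcome: 4.9%.

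**4. If main effects were also read as findings** (T0–T1 correlation assumed 0.5).
- Five outcomes, group or interaction: 39.9% down to 24.2% over correlations 0 to 0.8.
- Five outcomes, any of the three terms: 53.2% down to 33.8%.
- BIS-11 and DAQ-SF only, correlation 0.5, any term: 25.1%.
- With a common change of 0.3 SD in both arms (assumed) and no treatment effect, some term is significant in 59% of runs for one outcome, and in 91% for five outcomes at correlation 0.5.

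**5. Efficiency of the contrast.** Let rho be the T0–T1 correlation (not given) and σ² the variance at each time.
- Group by time is a t-test on change scores, with per-patient variance 2σ²(1 − rho).
- ANCOVA on T1 adjusted for T0 has residual variance σ²(1 − rho²).
- Ratio: (1 − rho²)/[2(1 − rho)] = (1 + rho)/2.

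| rho | Ratio | Variance saved | Power, change score | Power, ANCOVA |
|---|---|---|---|---|
| 0.3 | 0.65 | 35% | 0.65 | 0.83 |
| 0.5 | 0.75 | 25% | 0.79 | 0.89 |
| 0.7 | 0.85 | 15% | 0.95 | 0.97 |
| 0.9 | 0.95 | 5% | 1.00 | 1.00 |

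Power is for 25 per arm, two-sided 0.05, and a true T1 difference of 0.8 SD. One-tailed at rho 0.5 it is 0.87 against 0.94.

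**The case against.** Several stronger readings are tempting, and the text does not carry them.

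- A reader might infer that any effect on any of the five outcomes falls under the follow-up rule. The quoted rule covers four instruments, two of them primary. EEG has a similar rule of its own, drug use has a different analysis, and none is named for go/no-go.
- A reader might infer that a main effect counts as success. The text says only that it leads to post hoc tests. Followed up by level, a shared time effect would show both arms improving, and a careful analyst would see that. The large rates in step 4 therefore hold only on that inferred reading.
- A reader might infer testing at 0.05 for each outcome with no adjustment. No testing level is stated for the outcomes, and a multiplicity rule may sit in an analysis plan that is not shown. Its absence here is no finding.
- A reader might put the error rate at about 20% or more. That holds only for weak correlation, and the Introduction itself describes impulsivity and craving as closely related.
- A reader might take the T0/T1 repeated measures analysis to be wrong. The group-by-time test is valid under randomisation, and at rho 0.5 it exceeds the planned power in the one-tailed form for 0.8 SD.

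These limits stand. They leave untouched the printed conflict between outcomes and objectives, and the follow-up rule that does not single out the treatment contrast. An analysis plan could not settle either without overruling this text.

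**Conclusion.** The point holds, as a should-fix. The Objectives section contradicts itself on what is primary, and the RCT analysis lets main effects of time or group prompt follow-up on the same footing as the interaction.

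If all five primary outcomes were tested at 0.05, the chance of at least one false-positive treatment contrast is about 13% to 23%. For the two primary outcomes explicitly under the quoted rule it is about 8% to 10%. Both ranges rest on the assumed 0.05 per outcome and on correlations from 0.8 down to 0. The rate rises further only if main effects are taken as findings, which the document does not say.

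The ANCOVA suggestion is a separate, optional gain whose size depends on an unstated T0–T1 correlation.

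The EEG wording needs care. If the analysed quantity were a change score, the condition effect would be the treatment contrast, but the text does not say so. As written, time is missing from the listed factors.

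**What to change.** 1. **Name the contrast.** In the RCT analysis, state that for DAQ-SF and BIS-11 (and IFTE and IFTE-SR) only the randomised group contrast is evidence of a neurofeedback effect, and that main effects of time or group are descriptive. For EEG, add time to the model so that the treatment test is group by time, or use a baseline-adjusted group contrast.
2. **Use the T0 score.** Estimate the contrast by ANCOVA on the T1 score, adjusted for the same measure at T0. This targets the same treatment effect as group by time under randomisation, but it is a different and usually more precise estimator. The T0 data are already collected.
3. **Reconcile outcomes with objectives.** Designate one primary outcome and order the others as secondary. DAQ-SF craving matches the abstract's main objective, but the choice belongs to the investigators: the primary objective also includes drug use, and the Discussion opens with impulsivity. If all five stay primary, test them with Holm (smallest p-value against 0.05/5 = 0.01), with one test defined for each outcome, including a single go/no-go score of the investigators' choosing.

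**Cost.** Wording only; no new data or patients. The other outcomes lose stand-alone primary status, or under Holm each faces a stricter threshold. If craving is chosen, floor effects are a risk, since the Discussion warns that patients in early remission may report none.

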Several studies have shown neurofeedback to be a promising intervention for various disorders, ranging from SUD to attention deficit hyperactivity disorder (ADHD) [16]. In SUD, a widely used neurofeedback protocol is the Scott-Kaiser modification of the Peniston Protocol, consisting of a combination of sensorimotor rhythm feedback (SMR, 12-15 Hz) followed by alpha-theta based feedback [17]. With this type of protocol, patients first receive neurofeedback that focuses on reinforcing SMR (12-15 Hz) while inhibiting slower frequencies such as delta (2-5 Hz) and theta (5-8 Hz) and also inhibiting high beta (ranging from 18-30 Hz) [15,17]. This type of feedback is first employed for 10 to 20 sessions before the neurofeedback protocol is switched to an alpha-theta based protocol, where alpha (ranging from 8-12 Hz) is decreased while theta (5-8 Hz) is augmented until the amplitude of alpha drops below the level of theta [15,17]. The Scott-Kaiser modification of the Peniston Protocol has shown to be effective in opiate-dependent patients as well as in patients with a mixed substance dependency, as it led to the reduction of feelings of craving [15], a powerful predictor of relapse in drug-taking [20-21] and therefore promoted treatment attendance and abstinence rates of participants [17]. As most criminal offenders with SUD also suffer from comorbid psychiatric conditions however, treatment with neurofeedback may become more complicated [16]. For patients having a combination of impulsivity issues due to comorbidity with other psychiatric disorders, as well as substance abuse problems, it is suggested that an SMR-enhancing neurofeedback protocol should be applied to address the issue of impulsivity first [22]. Studies performing a neurofeedback protocol consisting of suppressing slow waves such as theta (4-7 Hz) and enhancing faster waves such as SMR (12-15 Hz) have demonstrated an improvement of impulse control in a population of students (in Egner and Gruzelier [23], for example) and have shown to positively affect motor control and cortical inhibitory function (in Sokhadze et al [16], for example). This type of neurofeedback protocol is also commonly applied with patients suffering from the hyperactive-impulsive ADHD subtype, and there are many studies reporting reduction in impulsivity after treatment (in Fuchs et al [24], for example). Several studies have shown that impulsivity and craving for substances are strongly correlated no matter the administered drug of choice. For example, in a study by Tziortzis et al [25] with methamphetamine users, individuals with higher levels of impulsivity reported significantly more craving than individuals scoring lower on impulsivity. In alcohol-dependent patients, higher scores of craving were correlated with higher self-reported impulsivity on the BIS-11 [26]. Moeller et al [27] found a significant correlation between the motor impulsivity subscale of the BIS-11 and craving in a population of cocaine-dependent subjects. Also for cocaine-dependent patients, higher impulsivity was associated with greater severity of addiction symptoms such as craving [28,29]. Also, contemporary neuropsychological models stress impulsivity and SUD to be the result of the same imbalance between bottom-up and top-down neural systems [30,31]. Bottom-up systems concern subcortical brain circuitry promoting impulsive reward behavior (regardless of long-term outcomes), whereas top-down processes concern reflective and self-control functions driven by prefrontal brain circuitry [32]. Within SUD, chronic substance abuse may produce neural changes leading to a structural state of disinhibition and impulsivity [33,34], causing immediate reaction to substance-related cues that elicit craving [35]. Not only acute but also prolonged effects of substance abuse have proven to be of great influence in disrupting these neuropsychological mechanisms, therefore maintaining problems with inhibitory control even after drug use is terminated [36]. Although impulsivity and craving are both independently identified as key elements in SUD, to date, there has been no study investigating whether a reduction in one will also lead to a reduction of the other.

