
### This Study

Although the relationship between impulsivity and symptoms of SUD such as craving and actual drug use has been established, to date there is no evidence about the effects of an impulsivity-based neurofeedback protocol and its effectiveness on impulsivity and on symptoms of SUD. This study aims to examine the treatability of impulsivity with an SMR-neurofeedback intervention in a population of forensic psychiatric patients with SUD and comorbid Axis I and/or II disorders. It also aims to investigate whether a reduction of impulsivity through an SMR-based neurofeedback protocol will also result in a reduction of SUD symptoms such as craving and actual drug use.

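### The primary objective asks whether reduced impulsivity carries the effect on craving and drug use, but the only analysis linking them tests moderation, with drug use as the dependent variable

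*Protocol article*

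**What the plan says.** Three places in the protocol article pose the same chain.

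- Abstract, Objective: "to what extent a reduction in impulsivity by a sensorimotor rhythm (SMR)-neurofeedback intervention will lead to a reduction in craving".
- This Study: "whether a reduction of impulsivity through an SMR-based neurofeedback protocol will also result in a reduction of SUD symptoms".
- Objectives (primary): "To what extent does a reduction in impulsivity by using SMR-neurofeedback result in a reduction of core symptoms of SUD", with craving and actual drug use named as those symptoms.

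The introduction gives the gap to be filled: there has been "no study investigating whether a reduction in one will also lead to a reduction of the other". The direct effects of neurofeedback on impulsivity, craving and drug use are listed separately, as secondary objectives 1 to 3.

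The Randomized Controlled Trial part of Statistical Analysis has two relevant pieces. Separate time-by-group analyses are planned for the DAQ-SF, BIS-11, IFTE and IFTE-SR. Then: "A repeated measures analysis of covariance will be conducted to examine differences in actual drug use as dependent variables", and the sentence ends "to test for a moderating effect of impulsivity on craving and actual drug use". No indirect-effect analysis is stated anywhere.

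**The concern.** The objective says that neurofeedback lowers impulsivity and that the lower impulsivity then lowers craving and use. That is mediation. The stated analysis is moderation, which asks for whom the effect is larger or smaller. The two can disagree completely: a treatment may act wholly through impulsivity with no interaction, or its effect may vary with impulsivity without changing impulsivity at all.

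The sentence is also inconsistent in itself. Its dependent variable is drug use, yet it announces a finding on craving, which is the only symptom named in the abstract's objective.

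Followed as written, the trial would answer its secondary objectives on impulsivity and craving but not its primary one. A null moderation result could be read as evidence against a hypothesis that is true, and a positive one as support for a hypothesis that is false.

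**Working it through.** **Matching analyses to objectives.** The article does not map them explicitly, so this is inferred.

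- The time-by-group analyses of BIS-11 and DAQ-SF match secondary objectives 1 (its BIS-11 part) and 2. Each handles one scale and does not relate the scales to each other.
- The analysis of covariance is the only one with drug use as dependent variable and the only one that brings in impulsivity. By elimination it is the one candidate for the primary objective.

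**The plan's own sample size.** Participants gives 1-tailed alpha 0.05, power 0.80, effect size 0.80 and 21 per condition. A two-sample one-sided t test with d = 0.80 has noncentrality 0.80 × √(21/2) = 2.59 on 40 degrees of freedom and power 0.817, so 21 is reproduced. (The article labels the effect size f; 21 follows only if 0.80 is read as d. That is a separate matter.) The figure sizes a simple two-group comparison, not an indirect effect.

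**Does moderation detect mediation?** The effects below are assumptions; the article gives none for these paths. Two-sided 0.05, 25 per arm, 4,000 simulated trials per setting, T0 values with SD 1:

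- impulsivity at T1 = 0.6 × T0 impulsivity − a × arm + 0.8 × noise
- craving at T1 = 0.5 × T0 craving + s × (change in impulsivity) + 0.7 × noise

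The whole effect runs through impulsivity and there is no interaction. With a = 0.8 and s = 0.5 the total effect on craving is −0.8 × 0.5 = −0.40.

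The moderation test is arm × T0 impulsivity or arm × impulsivity change. The mediation test requires both paths to be significant: arm to T1 impulsivity given T0 impulsivity, and T1 impulsivity to T1 craving given arm and both T0 values.

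| a | s | moderation rejects | mediation rejects |
|---|---|---|---|
| 0.8 | 0.5 | about 5% | about 88% |
| 0.8 | 0.3 | 4% to 5% | about 57% |
| 0.5 | 0.5 | about 5% | about 55% |
| 0.5 | 0.3 | about 5% | 33% to 35% |

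The 5% follows by construction, because no interaction was simulated. That is the point: full mediation does not imply an interaction, so the moderation test has nothing to find.

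**A second model, on change scores,** shows both directions of error.

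- Full mediation (0.8 and 0.5): moderation rejects in 5.0% (T0 impulsivity) and 5.1% (change); mediation in 76.5%.
- Moderation only (interaction 0.8 with T0 impulsivity, no effect on impulsivity): the test on T0 impulsivity rejects in 74.1%; mediation in 0.15%.

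**Which T0 values the craving model needs.** In the first model at a = 0.8, s = 0.5, the arm coefficient given T0 craving and T1 impulsivity is −0.24, although no direct effect exists. It becomes 0.00 only when T0 impulsivity is added. The outcome model for mediation must therefore contain T0 BIS-11.

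**The case against.** **The article is condensed and may contain a slip.** Moderating may have been written for mediating, and detailed mediation modelling is often left to an analysis plan. Both are fair. But the article does not leave the point open: it names a model, a dependent variable and an effect type. Reading the word as mediating does not rescue the sentence. An analysis of covariance of drug use gives no indirect effect and nothing on craving. With T0 impulsivity as covariate it says nothing about a reduction; with T1 impulsivity or its change it yields an adjusted association.

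**The objective might mean parallel change,** with impulsivity falling and symptoms falling. The separate scale analyses would partly address that. But those effects are already the secondary objectives, and the wording in all three places has one reduction produce the other.

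**Two stronger readings are not supported.**

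- A reader might infer that the effect on craving would be adjusted away. It would not: the DAQ-SF has its own time-by-group analysis with no covariate stated. The risk could arise only for drug use, and only if post-T0 impulsivity enters the model. The article does not say which value enters, and its Covariates list contains neither BIS-11 nor go/no-go scores.
- A reader might infer that the mediator never precedes the outcome. As a general statement this is wrong. Drug tests run about every 2 weeks, BIS-11 and DAQ-SF are repeated at 12 months in the intervention group, and both are taken twice weekly in the n-of-1 series. It holds for BIS-11 and DAQ-SF in the two-arm comparison, where they are measured together at T0 and T1.

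**The power of a mediation test depends on assumed effects.** This stands, so a range is given and not one figure.

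**Conclusion.** The point holds as a mismatch between the primary objective and the one analysis that could serve it, together with an inconsistency over craving within that sentence. The failure of the moderation test is structural: with full mediation and no interaction it rejects at about its nominal 5% whatever path sizes are assumed. The gain from a mediation test is less certain, at about 33% to 88% with 25 per arm over reductions of 0.5 to 0.8 SD and slopes of 0.3 to 0.5, none of which is in the article.

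The randomized comparisons of BIS-11 and DAQ-SF are unaffected. Even after correction the indirect effect on craving will be associational. Arm is randomized but impulsivity is not, and mediator and outcome are measured at the same visits.

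**What to change.** Replace the analysis-of-covariance sentence with three items.

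1. **Total effects.** Effect of arm on T1 DAQ-SF and on drug use, each adjusted for its T0 value. No post-T0 impulsivity in these models.
2. **Mediation for craving.** T1 BIS-11 on arm and T0 BIS-11; T1 DAQ-SF on arm, T1 BIS-11, T0 BIS-11 and T0 DAQ-SF. Report the indirect effect with a bootstrap confidence interval.
3. **Mediation for drug use.** A model suited to the number of positive tests out of tests done, with the indirect effect derived for that model. A linear product of two coefficients does not suit such counts. State that tests between T0 and T1 precede the T1 BIS-11, so for these tests the time order runs against the hypothesis.

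Add two statements: the indirect effects are associational, because BIS-11 and DAQ-SF are taken together at T0 and T1 in the two-arm comparison; and the sample size was not set for them, with the power range above and its assumptions.

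The cost is a rewritten paragraph and a few lines of bootstrap code, using data already planned and no further patients. A mid-treatment BIS-11 and DAQ-SF in both arms would improve the time order for craving, but it is optional.
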